# The Effect of Catgut Embedding at Acupoints Versus Nonacupoints in Abdominal Obesity: Protocol for a Multicenter, Double-Blind, 16-Week Randomized Controlled Trial

**DOI:** 10.2196/46863

**Published:** 2023-07-10

**Keywords:** acupoint catgut embedding, nonacupoints, abdominal obesity, randomized controlled trial, protocol, waist circumference

## Abstract

**Background:**

Obesity is an increasing problem worldwide. The effective treatments for obesity mainly include diet, physical activity, behavioral intervention, pharmacotherapy, and bariatric surgery, which all have certain limitations. As a specific type of acupuncture therapy, acupoint catgut embedding (ACE) has gained substantial attention in the management of obesity in recent years. Previous studies suggested that ACE may be an effective obesity treatment. However, the evidence for the efficacy of ACE in abdominal obesity (AO) remains inadequate due to the paucity of high-quality studies.

**Objective:**

This study aims to investigate the difference in the effectiveness of catgut embedding at acupoints and catgut embedding at nonacupoints in patients with AO and to further validate the efficacy and safety of ACE for AO.

**Methods:**

This is a multicenter, double-blind, 16-week randomized controlled trial. A total of 92 eligible participants with AO will be randomly divided into 2 groups (1:1 allocation ratio). The ACE group will receive catgut embedding at acupoints and the control group will receive catgut embedding at nonacupoints. The intervention will be performed every 2 weeks for a total of 6 sessions. Follow-up will be performed every 2 weeks for a total of 2 visits. The primary outcome is waist circumference. Secondary outcomes include body weight, BMI, hip circumference, and the visual analog scale of appetite. Upon the completion of the trial, we will evaluate the effect of catgut embedding at acupoints or nonacupoints on obesity indicators in patients with AO. For treatment outcomes, an intention-to-treat analysis will be performed.

**Results:**

The start of recruitment began in August 2019 and is expected to end in September 2023.

**Conclusions:**

Although studies have been conducted to demonstrate the effectiveness of ACE in the treatment of obesity, the evidence for the efficacy of ACE in AO remains insufficient due to the quality of the studies. This rigorous normative randomized controlled trial will verify the effect of catgut embedding at acupoints or nonacupoints in patients with AO. The findings will provide credible evidence as to whether ACE is an effective and safe treatment for AO.

**Trial Registration:**

Chinese Clinical Trial Registry ChiCTR1800016947; https://tinyurl.com/2p82257p

**International Registered Report Identifier (IRRID):**

DERR1-10.2196/46863

## Introduction

Obesity has become a global health issue regardless of race, region, and age [1]. Globally, the prevalence of obesity in adults was approximately 13% (603.7 million). There were approximately 107.7 million children and adolescents who were obese [2,3]. The prevalence of obesity was about 20% or more in the United States, the Middle East and North Africa, the Caribbean, Polynesia, and Micronesia [4]. The increase of adults who are obese has leveled off in several high-income countries, but the incidence is dramatically on the rise in most low- and middle-income countries, particularly in urban regions [1,5]. As a major type of obesity, the prevalence of abdominal obesity (AO) in adults was 29.1% (28.6% in men and 29.6% in women) in China [6]. Obesity is a worldwide problem and a burden in many diseases [2,7,8]. Studies have demonstrated that obesity may lead to diabetes, subfertility, chronic spontaneous urticaria, nonalcoholic fatty liver disease, Alzheimer disease, cardiovascular diseases, and even cancer [2,9-18]. In addition to diseases, obesity can also affect disability-adjustment life-years and generate a large economic burden [4,19-21]. Obesity is also a persistent problem, where most children who are obese will remain obese in adolescence [22].

The effective treatments for obesity mainly include diet, physical activity, behavioral intervention, pharmacotherapy, and bariatric surgery [23-29]. Diet and physical activity require great self-discipline and enough time, which are difficult to adhere to. The effect of behavioral intervention for obesity is typically limited [30]. Side effects such as abdominal pain, vomiting, nervousness, insomnia, headache, dizziness, dysgeusia, and insomnia may accompany pharmacotherapy [31]. Pharmacotherapy could not be used for patients who are obese with complicated active cardiovascular disease, glaucoma, uncontrolled hypertension, anorexia, thyroid, and many other diseases [32,33]. For pregnant individuals and children, the safety of pharmacotherapy is still not guaranteed currently [34]. Bariatric surgery requires a high level of medical technology and may increase the risk of fractures [35-37]. Alternative therapies such as acupuncture, moxibustion, acupoint catgut embedding (ACE), and massage are increasingly used for the treatment of obesity [38-42].

ACE is a special acupuncture therapy that combined the absorbable surgical suture and acupoint, and the effective stimulation of every ACE treatment could persist for 2 weeks. Previous studies indicated that ACE was an efficient treatment for obesity, but the risk of bias was significantly high [43]. Therefore, this rigorous and normative randomized controlled trial (RCT) study is designed to verify the efficiency of catgut embedding at acupoints and nonacupoints in participants with AO. The findings will provide credible evidence as to whether ACE is an effective and safe treatment for AO.

## Methods

### Study Design and Setting

This multicenter, double-blind, 16-week RCT will be conducted from August 2019 to September 2023 in 4 clinical centers: The Second Affiliated Hospital of Yunnan University of Chinese Medicine, The Sports Trauma Specialist Hospital of Yunnan Province, Kunming Hospital of Traditional Chinese Medicine, and ShengAi Hospital of Traditional Chinese Medicine. A total of 92 eligible participants with AO will be assigned to 1 of 2 groups (catgut embedding at acupoints or nonacupoints) using central randomization (1:1 allocation ratio). Every participant will receive a 12-week intervention period and a 4-week follow-up. The flowchart of this study is shown in Figure 1.

**Figure 1 figure1:**
[figure not shown]
Flowchart of the trial. ACE: acupoint catgut embedding.

### Ethics Approval

This protocol is in line with the Declaration of Helsinki and has been approved by the Hospital Ethics Committee of The Sports Trauma Specialist Hospital of Yunnan Province (2018CK-001) in June 2018. The study has been registered in the Chinese Clinical Trial Registry (ChiCTR1800016947). This protocol is compliant with the principles of the SPIRIT (Standard Protocol Items: Recommendations for Interventional Trials; see Multimedia Appendix 1) and CONSORT (Consolidated Standards for Reporting Trials) guidelines [44]. The SPIRIT checklist is presented in Multimedia Appendix 1 and the schedule is shown in Table 1.

**Table 1 table1:** Study schedule for data measurements.

			Study period and time point (week)										
		Enrollment		Allocation	Treatment phase							Follow-up	
		–1		0	2	4	6	8	10	12	14		16
**Enrollment**													
	Eligibility screen	✓											
	Informed consent	✓											
	Physical examination	✓											
	Randomization			✓									
**Interventions**													
	ACE^a^ group (n=46)				✓	✓	✓	✓	✓	✓	✓		✓
	Control group (n=46)				✓	✓	✓	✓	✓	✓	✓		✓
**Assessments**													
	BW^b^	✓		✓	✓	✓	✓	✓	✓	✓	✓		✓
	BMI	✓		✓	✓	✓	✓	✓	✓	✓	✓		✓
	WC^c^	✓		✓	✓	✓	✓	✓	✓	✓	✓		✓
	HC^d^			✓	✓	✓	✓	✓	✓	✓	✓		✓
	VAS^e^ of appetite			✓	✓	✓	✓	✓	✓	✓	✓		✓
**Safety**													
	AE^f^				✓	✓	✓	✓	✓	✓			

^a^ACE: acupoint catgut embedding.

^b^BW: body weight.

^c^WC: waist circumference.

^d^HC: hip circumference.

^e^VAS: visual analogue scale.

^f^AE: adverse event.

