### Interventions

All catgut embedding manipulations will be performed by an acupuncturist with national medical qualifications. The participants will receive treatment every 2 weeks for a total of 6 sessions.

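### Table 1 schedules no adverse-event check at either follow-up visit (weeks 14 and 16), although all five efficacy measures are taken at both

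*Protocol article*

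**What the plan says.** The text describes the timetable consistently. The Interventions section states: "The participants will receive treatment every 2 weeks for a total of 6 sessions". Study Design and Setting states: "Every participant will receive a 12-week intervention period and a 4-week follow-up". The Abstract (Methods) adds: "Follow-up will be performed every 2 weeks for a total of 2 visits". Follow-up therefore consists of visits at weeks 14 and 16.

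Table 1 is the visit schedule. Its five assessment rows (body weight, BMI, waist circumference, hip circumference and "VAS^e^ of appetite") are ticked at every visit from week 0 to week 16. Its single safety row, footnoted "f^AE: adverse event", is ticked at weeks 2, 4, 6, 8, 10 and 12 and is empty at weeks 14 and 16.

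The Safety Evaluation section sets no visit schedule of its own. It expects mild local reactions 1 to 5 days after embedding. It also lists worse local events, including extrusion of the thread, liquefaction of fat and nerve injury, without saying when they may occur. For these it provides suspension of treatment, care until recovery and assessment through the study center. Serious or unexpected events are to be reported verbally within 24 to 48 hours.

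**The concern.** The Abstract's Objective names safety beside efficacy. The Introduction and Conclusions promise evidence on whether the treatment is safe, and Strengths and Limitations presents the trial as a study of both. A schedule that measures efficacy at two further visits but asks nothing about harms there serves the two aims unequally.

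The events at risk of being missed are non-serious ones of an expected type, such as persistent local reactions, that a participant does not volunteer. The 24-to-48-hour rule is limited to serious or unexpected events and does not cover them. Harm counts for the last four weeks could therefore be incomplete in both arms.

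This is not a detail left to a fuller document. The article prints a visit-by-visit safety schedule, and that schedule stops at week 12.

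**Working it through.** **Inputs.** Six sessions, two weeks apart (Interventions). 12 weeks of treatment and 4 of follow-up (Study Design and Setting). Tick positions (Table 1). Local reactions at 1 to 5 days (Safety Evaluation). 92 participants and 10% dropout (Sample Size Calculation).

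**1. The plan's own timetable.** Sessions: 12 / 2 = 6. Follow-up visits: 4 / 2 = 2. Both match the text.

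**2. Ticks aligned to the week header.**

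| Row | Weeks ticked after baseline | At weeks 14 and 16 |
|---|---|---|
| Each of five efficacy measures | 2, 4, 6, 8, 10, 12, 14, 16 | 2 of 2 |
| Adverse events | 2, 4, 6, 8, 10, 12 | 0 of 2 |

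The empty cells do not look like a loss in text extraction: the row keeps its trailing blank cells, and its six ticks line up with weeks 2 to 12.

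**3. What the gap leaves uncovered.** This depends on the session weeks, which the article does not state. The last scheduled check is week 12 (day 84) and the trial ends at week 16 (day 112), so 112 − 84 = 28 days have no scheduled check on either reading.

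*Sessions at weeks 0 to 10.*
- The last session is on day 70 and its expected reactions fall on days 71 to 75.
- The week 12 check comes 84 − 70 = 14 days after that session and 84 − 75 = 9 days after the reaction window closes.
- Sessions without a later scheduled check: 0 of 6.
- Days after the last session: 112 − 70 = 42, of which the final 28 have no scheduled check.

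*Sessions at weeks 2 to 12.*
- The last session is on day 84, at the same visit as the last check.
- Its expected reactions fall on days 85 to 89, after that check.
- Sessions without a later scheduled check: 1 of 6 (17%).
- All 28 days after the last session have no scheduled check.

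**4. Which reading is better supported.** Weeks 0 to 10. In Table 1, "Randomization" is ticked at week 0. Recruitment and Randomization has the envelope opened when treatment starts. Six two-week cycles beginning at week 0 fill the 12-week period exactly. The main evidence for weeks 2 to 12 is that the intervention ticks begin at week 2, in rows that are themselves misprinted (see the objection).

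**5. Visits affected.** At most 92 × 2 = 184. If the 10% dropout all occurs before week 14: 92 × 0.9 = 82.8, and 82.8 × 2 = 165.6, about 166. The 84 in Sample Size Calculation is the size before inflation for dropout, not a number of completers.

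**The case against.** The strongest reply is that stopping routine checks at week 12 is defensible. With sessions at weeks 0 to 10, the week 12 visit falls 14 days after the last session, well beyond the 1-to-5-day reactions. It also falls at the end of the two-week stimulation that the Introduction attributes to each treatment. Nothing in the article says that thread extrusion, fat liquefaction or nerve injury arises later than that, and suspending treatment when they occur places them mainly within the treatment period. This stands, and it makes the point small. It does not explain why two attended visits should record efficacy but ask nothing about harms.

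Three stronger inferences are tempting, and the documents support none of them.

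- *That harms go unrecorded after week 12.* The reporting route in Safety Evaluation has no end date and is not tied to visits. Only the scheduled question is absent.
- *That embedding continues through follow-up without safety checks.* Both intervention rows carry eight ticks, at weeks 2 to 16. The text gives six sessions and a 12-week treatment period, so the extra ticks are a clerical slip and no sign of how the trial is run.
- *That the comparison between arms is biased.* Both arms have the same schedule. Incomplete counts are possible, but no bias between arms is shown.

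**Conclusion.** The point holds as a minor weakness in the safety schedule. None of the two follow-up visits has a scheduled adverse-event check, while both have all five efficacy measures.

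The tick count is certain; its consequence depends on the unstated session weeks. On the better-supported reading (weeks 0 to 10), every session is followed by a check and the exposure is limited to later non-serious events in the last 28 days. On the other reading, one session in six has no later scheduled check. That delayed non-serious events occur at all is an assumption, since the article neither documents nor excludes them. The primary outcome, sample size and power are unaffected.

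**What to change.** Tick adverse events at weeks 14 and 16 in Table 1, ask about them at those visits, and include the events in the safety summary. The cost is one form page at up to 184 visits that already take place (about 166 with 10% dropout), plus a notification to the ethics committee. The article appeared in July 2023 and the trial is expected to end in September 2023, so the change helps only participants still in follow-up.

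When the table is revised, reduce both intervention rows to the six session weeks actually used, with none at weeks 14 and 16. The clinical team should confirm whether these are weeks 0 to 10 or 2 to 12, which would also settle how much the gap matters.

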### Participants

Participants who meet all the following criteria will be included: (1) aged between 18 and 60 years with simple obesity; (2) BMI ≥28 kg/m^2^ and waist circumference (WC) ≥90 cm for male participants and ≥85 cm for female participants; (3) agreed to participate in this study and signed written informed consent for this trial and catgut embedding therapy; and (4) did not participate in other trials within past 3 months. Participants will be excluded if they meet any one of the following criteria: (1) secondary obesity, such as obesity caused by endocrine disease (Cushing syndrome, thyroid disease, hypothalamic disease, pituitary disease, gonadal disease, etc) and medication (glucocorticoid or antipsychotics); (2) pregnancy, lactation, and childbirth within the past 6 months; (3) heart disease; hematopoietic system, liver, kidney, and other important organ diseases; and hypertension that is not effectively controlled; (4) severe mental and neurological diseases where the patient is unable or unwilling to cooperate; (5) allergy to alcohol and animal protein or immune diseases; and (6) received other weight loss treatment within the past 3 months.

### Criteria for Elimination From the Study

Those who meet the following criteria should be eliminated from the study: (1) misdiagnosis and misrepresentation; (2) poor treatment tendency; (3) involvement with other treatments after being selected; and (4) participants’ withdrawal before the first test recording.

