### Recruitment and Randomization

All participants with eligible AO will be recruited from the 4 hospitals and the community. Recruitment methods mainly include posters, public notice boards, and WeChat public numbers in hospitals and communities. The randomization sequence will be generated by the Clinical Research Center of Yunnan University of Chinese Medicine using a computerized random number generator and placed in opaque envelopes. Stratified randomization will be performed for the 4 clinical centers. To ensure allocation concealment, randomization will be performed by an independent researcher. The research assistant will open the envelope when the participant begins treatment to determine the assigned group and will not disclose grouping information under any circumstances. The acupuncture therapist will be responsible for manipulation only.

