### Blinding and Informed Consent

Participants will be informed that they have a 1 in 2 chance of being assigned to 1 of 2 treatments: catgut embedding at acupoints or nonacupoints. The procedure and stimulation of the catgut embedding at acupoints are identical to catgut embedding at nonacupoints. Therefore, participants will be blinded to their treatment assignment. Both groups of participants will be assigned to different treatment rooms to prevent intercommunication. In addition, the acupuncturist, outcome assessor, and those involved in data collection and statistics will be blinded to treatment assignment throughout the trial. Research assistants with knowledge of grouping information will be asked not to communicate with participants or outcome assessors regarding treatment procedures and responses. All patients will be fully informed about the study (including the purpose of the trial and possible risks, etc) prior to participation in the trial, and they have the right to withdraw from the trial at any time without giving a reason. They will sign a written informed consent for voluntary participation prior to enrollment.

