### Statistical Analysis

All data will be analyzed by SPSS statistical software (version 19.0; IBM Corp). The clinical outcomes and baseline characteristics are based on the intention-to-treat population, which will include participants who have received at least one treatment. Continuous variables will be shown as the mean and SD, whereas the nonnormally distributed variables will be presented as the median and IQR. Categorical variables will be described as numbers and percentages. The normality of continuous variables will be determined using the Shapiro-Wilk test, Kolmogorov-Smirnov test, skewness, and kurtosis. The homogeneity of continuous variables will be determined by *F*-test, Brown-Forsythe, and Bartlett tests. Comparisons between groups will be made using independent samples 2-tailed *t* tests or nonparametric tests (Mann-Whitney *U* test). Repeated measures within groups (≥3) will be analyzed using one-way ANOVA or nonparametric (Friedman) tests. Paired 2-tailed *t* tests or nonparametric tests (Wilcoxon test) will be used for within-group pre-post comparisons. For categorical data, the chi-square test will be used to assess the significance of differences. Values of *P*<.05 will be considered significant using a 2-sided test.

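### The promised intention-to-treat analysis is defined as a treated-at-least-once set and conflicts with a rule that eliminates participants from the study for events that can follow randomisation

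*Protocol article*

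**What the plan says.** The Abstract (Methods) states: "For treatment outcomes, an intention-to-treat analysis will be performed". Statistical Analysis bases the clinical outcomes and baseline characteristics on the "intention-to-treat population, which will include participants who have received at least one treatment".

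Criteria for Elimination From the Study is a section of its own, placed after the eligibility criteria under Participants. It opens: "Those who meet the following criteria should be eliminated from the study: (1) misdiagnosis and misrepresentation". The list continues "2) poor treatment tendency; (3) involvement with other treatments after being selected" and ends with criterion (4), "withdrawal before the first test recording". The article does not say what criterion (2) means, who decides on elimination, whether that person is blinded, or whether an eliminated participant stays in follow-up or in the analysis.

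Two other sections bear on the point. Under Recruitment and Randomization, "The research assistant will open the envelope when the participant begins treatment to determine the assigned group". Under Blinding and Informed Consent, participants, acupuncturist, assessors and statisticians are blinded, while "Research assistants with knowledge of grouping information will be asked not to communicate with participants or outcome assessors".

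**The concern.** An ITT comparison keeps everyone randomised in the arm assigned, because only that set has the comparability that randomisation creates. The article departs from this in two ways.

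First, the set it calls ITT requires at least one treatment. That is a modified ITT set under the wrong name.

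Second, the elimination rule can take randomised participants out of the trial. Strengths and Limitations says that diet and exercise are left alone, so a participant who sees little change in waist circumference (WC) has an evident reason to look for another weight-loss treatment. That would meet criterion (3). Poor compliance or poor response, either of which might be what criterion (2) means, could also follow disappointing results. If such participants are removed, or simply stop being measured, those who remain are a selected group. If the selection differs between arms, the primary comparison is biased.

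**Working it through.** **Step 1: set the rules side by side.** The table shows what each section implies for a randomised participant.

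| Participant | Statistical Analysis | Elimination criteria |
|---|---|---|
| Randomised, never treated | Not in the ITT set | Covered by (4) only if withdrawn before the first recording |
| Treated once, then takes another treatment | In the ITT set | Eliminated under (3) |
| Treated, judged to meet (2) | In the ITT set | Eliminated under (2) |

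The second and third rows conflict: one section keeps the participant and the other removes them.

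**Step 2: timing.** In Table 1, screening and consent are at week -1, randomisation is at week 0, and visits run every 2 weeks from week 2 to week 16. Criterion (3) applies from selection onward with no end date, so it covers the whole period after randomisation. Criterion (2) reads most naturally as a judgement made during treatment. Criterion (1) concerns eligibility. Criterion (4) depends on which recording counts as the first, and this is not stated.

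**Step 3: the plan's own figures.** No figure in the article measures this effect. The only attrition figure is the 10% dropout allowance under Sample Size Calculation. Applied to 46 per arm it gives 0.10 × 46 = 4.6, or about 5 participants. It is used below only as an assumed elimination rate.

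**Step 4: illustration of possible bias.** Assume normal outcomes with SD 1, 46 per arm, no true difference and a two-sided t test at 5%. Participants with the lowest values of a latent score are removed, and ρ is the correlation of that score with outcome. Removing a fraction p from one arm shifts its mean by about

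ρ × φ(z) / (1 − p), where z is the normal quantile at 1 − p.

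For p = 0.10 and ρ = 1, z = 1.2816 and the shift is φ(1.2816)/0.9 = 0.195 SD. For ρ = 0.5 it is about 0.10 SD. Simulation with at least 20,000 trials per row gave:

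| Removed, arm A / arm B | ρ | Shift in difference (SD) | Rejection rate |
|---|---|---|---|
| 3 / 2 | 0.5 | 0.02 | 5–6% |
| 5 / 5 | 0.5 | 0 | about 6% |
| 5 / 0 | 0.3 | 0.06 | about 6% |
| 7 / 2 | 0.5 | 0.09 | 7–8% |
| 5 / 0 | 0.5 | 0.10 | about 8% |
| 5 / 5 | 1 | 0 | 8–9% |
| 7 / 2 | 1 | 0.18 | about 18% |
| 5 / 0 | 1 | 0.20 | about 18% |

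In the row with 5 removed from each arm at ρ = 1, the mean difference is unbiased. The error rate rises because trimming both arms makes the SD too small.

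**The case against.** The strongest reply is that elimination is from the study, not expressly from the analysis. Only Statistical Analysis defines an analysis population, and read literally it keeps anyone treated once. That is fair: the text does not establish that eliminated participants are dropped from the analysis. It does not settle the matter, because elimination from a study would ordinarily end measurement, and the article nowhere says that these participants continue. Their later WC values could be lost even if they stay in the analysis set by name. A condensed article may leave details to the full protocol, but the two rules it does state conflict.

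Four stronger readings are tempting and are not supported:

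- **That participants are eliminated for outcome-related reasons.** Criterion (2) is undefined and may mean compliance. Criterion (3) could also be met between screening and randomisation. Criteria (1) and (4) are not clearly tied to outcome. A link with response is plausible for (2) and (3), but it is an inference.
- **That the treated-at-least-once limit is itself a serious source of bias.** The envelope is opened when treatment begins, and participants and the acupuncturist are blinded. Few participants should have a known allocation and no treatment, so this part is mainly a labelling error.
- **That unblinded staff will skew elimination.** Research assistants know the allocation, but nothing says that they decide on elimination. The gap is that no decision-maker and no blinding of the decision are stated.
- **That the error rate is 18%, or the bias 25% of the planned difference.** The first is the extreme case of one-sided removal of exactly the worst outcomes. The second is 0.195 × 0.31 = 0.060 kg/m², divided by 0.24 kg/m². It makes the same extreme assumption and is on BMI, a secondary outcome. The article gives no planned difference or SD for WC.

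**Conclusion.** The point stands. The article promises ITT, defines a modified ITT set, and states an elimination rule that cannot be followed together with that definition. Following the elimination rule would lose randomised participants, or their outcome data, from the primary comparison for events that can arise after randomisation and may be related to response.

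The conflict rests on the text alone. The size of any bias does not: it depends on how many are eliminated, how unequally between arms, and how strongly elimination tracks outcome, and the document gives none of these. At an assumed elimination of about 10%, the error rate stays near 5–6% when numbers are similar in both arms with moderate correlation, or when the correlation with outcome is weak. It is about 8% for one-arm elimination at correlation 0.5, and about 18% only for one-arm elimination at correlation 1. With participants blinded and the two procedures described as identical, nothing in the document points to that extreme.

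**What to change.** 1. Define the primary analysis set as all randomised participants, in the arm assigned.
2. State that events on the elimination list are recorded as protocol deviations and do not remove a participant from follow-up or from the primary analysis. WC continues to be measured at the scheduled visits where the participant consents.
3. Define criterion (2) and have it judged by someone blind to allocation.
4. Exclude participants meeting (2) or (3) only in a per-protocol analysis, reported as a sensitivity analysis.
5. Call the treated-at-least-once set modified ITT.
6. Keep participants under (4) in the randomised set and state a missing-data approach, since they may have no post-baseline values. Say which recording counts as the first.

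Whether and when treatment stops after such an event is for the investigators. They should reconcile the elimination criteria with Statistical Analysis, and this point proposes no clinical rule.

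The cost is wording in those two sections, measurements at visits already in Table 1, and possibly a slightly diluted estimate from keeping participants who did not adhere. Recruitment was expected to end in September 2023, so continued measurement helps only participants still within their 16 weeks. For anyone eliminated before that, the measurements already held and the missing-data approach have to serve.
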